### Washout Period

The purpose of the 21-day washout period is to mitigate or minimize any potential carryover effects from the intervention. The term *carryover effect* refers to the persistence of the previous intervention’s effect or the impact of the initial intervention that extends beyond its duration and influences the subsequent intervention’s effect. By incorporating a washout period, we aim to ensure a clearer distinction between the effects of each intervention and minimize any potential interference or bias [24].

The available evidence on determining the appropriate washout period to eliminate the carryover effect effectively is limited. The conventional approach for determining the washout period is often based on the concept of 5 half-lives of the specific drug involved [25]. To address the carryover effect in this study, we used 2 strategies. First, we implemented a washout period of 21 days between interventions. This time gap was intended to allow for a sufficient delay to minimize the memory of the previous intervention and any lingering effects from the previous intervention. In addition, for the second intervention, the investigators carefully selected a different topic from the assignment to ensure that students would not easily recall specific details from the previous intervention. Furthermore, the research team ensured that the assignment content for the second intervention had similar complexities and requirements to maintain consistency across the study.

### Outcomes and Measurements

The outcome measures will be (1) the usability of the technological tools (ChatGPT or conventional) for completing the assignments (primary outcome), (2) the participants’ perception of these tools as support for learning, and (3) the learning outcomes (secondary outcomes). Outcomes and measurements will be collected at 2 points: at the first follow-up, that is, after the first intervention (experimental or control) in the initial phase, and at the second follow-up, that is, after the second intervention (experimental or control) in the final phase (Figure 1).

#### Usability

Participants in the experimental intervention (AI-ChatGPT intervention) will also be asked to fill out a survey regarding their perception of using generative AI as an assistance tool to complete their assignments. This survey aims to gather insights into their thoughts, opinions, and attitudes toward using AI in their learning experiences. Participants will have the opportunity to share their feedback on the effectiveness, benefits, challenges, and overall satisfaction while using AI for assignment completion. Their responses will provide valuable information on AI technology’s perceived value and acceptance in enhancing their learning experience. Participants in the control intervention (conventional tools) will complete the same survey, but regarding the usability of the conventional tools.

The System Usability Scale (SUS) will assess the participants’ perceptions of usability. The SUS is a valid questionnaire [26] and will be administered at the end of the interventions and when participants cross over to the other assistance tool (AI-ChatGPT or conventional web-based tools without AI). The SUS is commonly used in numerous studies to assess the effectiveness and usability of new technologies, including in the education field [27-29]. A recent systematic review of home-based telerehabilitation software systems for remote supervision revealed that the SUS tool was the most frequently used measure or tool across the studies examined [28]. This scale has been translated into several languages, including the American Sign Language [30-32]. The SUS questionnaire was originally developed as a “quick and dirty” tool, with the goal of providing a fast and nonintrusive assessment experience for participants [26]. The SUS consists of 10 items formulated as affirmative statements, for which users indicate their level of agreement or disagreement on a 5-point Likert scale (1=strongly disagree; 5=strongly agree). For the odd answers (1, 3, and 5), we will subtract 1 from the score that the user answered; for the even answers (2 and 4), the score will be subtracted from 5. The values of the 10 questions will be added and multiplied by 2.5. The final score can range from 0 to 100. Internal consistency will be calculated using Cronbach α per item and overall. This scale allows for the assessment of outcomes and comparisons within and between the 2 interventions (Table 1).

**Table 1 table1:** Overview of outcome measures.

Outcome measure		Variable or scale	Measure	Analysis method

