**Primary**				
	Usability (SUS^a^)	Continuous, nominal, ordinal, and 5-point Likert-type scale^b^	0-100 (SUS score: >68=above average and <68=below average) The individual scores of the participants for each question are transformed into a new number, which is then aggregated and multiplied by 2.5 to convert the initial range of scores from 0-40 to a new range of 0-100.	The frequencies, means, and SD of each item of the SUS scale will be calculated and compared using the McNemar or chi-square and Wilcoxon tests, respectively. In addition, each group’s usability scores and grades will be correlated using Spearman correlation.

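### The SUS scoring rule for the primary outcome is misstated: it recodes by the answer given rather than by item number, so the total score is wrong if the rule is applied as written

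*Protocol article*

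**What the plan says.** The rule is in the protocol article under Outcomes and Measurements, Usability. The instrument is described thus: "The SUS consists of 10 items formulated as affirmative statements", each answered on a "5-point Likert scale (1=strongly disagree; 5=strongly agree". The recode follows in two halves. The first half reads: "For the odd answers (1, 3, and 5), we will subtract 1 from the score that the user answered". The second half, which runs in the opposite direction, reads: "for the even answers (2 and 4), the score will be subtracted from 5". Then: "The values of the 10 questions will be added and multiplied by 2.5", and "The final score can range from 0 to 100".

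Table 1 repeats the structure without the recode. It says "The individual scores of the participants for each question are transformed into a new number", and that the multiplication serves to "convert the initial range of scores from 0-40 to a new range of 0-100".

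Neither place gives a rule by item number, lists the items or says which are reverse-scored. Outcomes and Measurements names usability as the primary outcome. Data Analysis compares the usability scale by the Wilcoxon test, correlates it with grades and with perception by Spearman's coefficient, and splits it at 50. Table 1 also gives a benchmark of 68.

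**The concern.** The bracketed numbers are exactly the five response options just defined, and the rule speaks of answers, not items. Read that way, the direction of scoring switches from one response category to the next within the same item. No item, favourable or unfavourable, can sensibly be scored so. Two opposite recodes (response minus 1, and 5 minus response) make sense only if each belongs to a different set of items.

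At stake is the definition of the primary outcome. Anyone who programmed the sentence literally would carry the error into the Wilcoxon comparison of totals, the Spearman correlations and both cut-offs.

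**Working it through.** **Inputs** (Usability section and Table 1): 10 items; responses 1 to 5; odd answers become x − 1; even answers become 5 − x; total = 2.5 × sum; stated range 0 to 100 from a raw sum of 0 to 40.

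**1. The mapping as written.** f(1) = 1 − 1 = 0; f(2) = 5 − 2 = 3; f(3) = 3 − 1 = 2; f(4) = 5 − 4 = 1; f(5) = 5 − 1 = 4.

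**2. The plan's own range.** Minimum 2.5 × 10 × 0 = 0; maximum 2.5 × 10 × 4 = 100. The stated range reproduces, so it is no evidence against the literal rule and offers no safeguard either.

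**3. The order of responses.** The same answer to all 10 items gives 2.5 × 10 × f(x):

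| Answer to all items | Total as written |
|---|---|
| 1 | 0 |
| 2 | 75 |
| 3 | 50 |
| 4 | 25 |
| 5 | 100 |

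The three middle categories are in reverse order relative to the two ends.

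**4. Brackets read as item numbers.** Only items 1 to 5 then have a rule, and they contribute 0 to 20. If items 6 to 10 are left out, the total runs from 0 to 2.5 × 20 = 50. If they enter raw (5 to 25), it runs from 2.5 × 5 = 12.5 to 2.5 × 45 = 112.5. Neither agrees with 0 to 100.

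**5. Consequence if items alternate in direction (assumption).** A consistent respondent who answers x on odd-numbered items answers 6 − x on even-numbered ones. From step 1, f(x) + f(6 − x) = 4 for every x: 0 + 4, 3 + 1, 2 + 2, 1 + 3, 4 + 0. Five such pairs give 5 × 4 × 2.5 = 50.

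| Odd / even items | Scored by item number | Scored as written |
|---|---|---|
| 5 / 1 | 100 | 50 |
| 4 / 2 | 75 | 50 |
| 3 / 3 | 50 | 50 |
| 2 / 4 | 25 | 50 |
| 1 / 5 | 0 | 50 |

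All five fall exactly on the cut-off of 50 and below the benchmark of 68.

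Real answers need not mirror each other. Suppose even-numbered items stay at 2 and odd-numbered items improve from 3 to 4. By item number the total rises from 2.5 × 5 × (2 + 3) = 62.5 to 2.5 × 5 × (3 + 3) = 75. As written it falls from 2.5 × 5 × (2 + 3) = 62.5 to 2.5 × 5 × (1 + 3) = 50. A gain of 12.5 becomes a loss of 12.5.

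**6. Simulation for scale (illustrative; the response model is an assumption).** With alternating items and equal agreement levels on both item types, the written total had a correlation of about 0.00 with the item-number total. A true shift of 9 to 11 points moved it by about 0. With unequal agreement levels, the correlation ran from about −0.66 to 0.66, and a true shift of 8 to 11 points moved the written total by about −4 to +6.

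**7. Consequence if all items run in one direction.** The correlation of the written total with underlying usability was 0.41 to 0.82, depending on how strongly the items reflect it, against 0.83 to 0.95 for plain x − 1 scoring. A true shift of about 9 to 11 points moved the written total by about 6.

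**The case against.** This may well be a slip of wording. The article names an established questionnaire with its source, gives the transform, sum and multiply structure, and cites a benchmark of 68, so the intended instrument can be identified. Nothing shows that wrong scoring was or will be run, and raw item responses allow a correction without loss. All of this stands, and it makes the repair cheap. It does not make the sentence right: the article states a rule, the rule is wrong on either reading, and no other section corrects it.

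A reader might go further and infer that the score cannot measure usability at all, or that a real difference between the tools would go unseen. The article does not support that:

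- The exact cancellation at 50 needs items that alternate in direction and answers that mirror each other. The article lists no items and does not state their direction.
- Step 6 shows that a correlation of zero is one symmetric case, and step 7 that a one-directional questionnaire would give a distorted score, not an empty one.
- Table 1 and Data Analysis also plan comparisons of each SUS item. On raw responses these do not depend on the recode. The text does not say whether they, or Cronbach α, use recoded values.

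Nor can the stated range be cited against the literal rule; it conflicts only with the item-number reading of the brackets. A power figure would need a response distribution, a standard deviation and a within-person correlation that the article does not give, so none is offered.

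**Conclusion.** Wrong as written. From the article alone, the stated rule ranks *disagree* (75 if given throughout) above *agree* (25 if given throughout), and the alternative reading leaves half the items unscored. That much needs no assumption.

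The consequence is conditional on two things: that the rule is applied literally, and the direction of the items. With alternating items, which the two opposite recodes suggest but the article does not state, a true difference in the total is largely lost or can change sign, depending on response levels. With items all in one direction, the total is seriously distorted. The effect reaches the Wilcoxon comparison of totals, the Spearman correlations and the cut-offs of 50 and 68. Item-level comparisons on raw responses are untouched.

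**What to change.** Replace the recode sentence with a rule by item number: odd-numbered items (1, 3, 5, 7, 9) contribute response minus 1; even-numbered items (2, 4, 6, 8, 10) contribute 5 minus response; sum the 10 contributions and multiply by 2.5. Confirm this against the item wording of the questionnaire used, and list the reverse-scored items. State whether the item-level tests and Cronbach α use raw or recoded responses.

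Then check the scoring syntax. A simple test is to run the five patterns in the second table of the working: if the questionnaire alternates, they should return 100, 75, 50, 25 and 0. A check that totals lie between 0 and 100 is not enough. If the syntax follows the printed rule, re-score from the raw responses before results are reported.

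The cost is a corrected sentence or two and a syntax check. The Results section says that data collection took place in October and November 2023; no new data are needed, and the sample size does not depend on this point.

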**Primary**				
	Usability (SUS^a^)	Continuous, nominal, ordinal, and 5-point Likert-type scale^b^	0-100 (SUS score: >68=above average and <68=below average) The individual scores of the participants for each question are transformed into a new number, which is then aggregated and multiplied by 2.5 to convert the initial range of scores from 0-40 to a new range of 0-100.	The frequencies, means, and SD of each item of the SUS scale will be calculated and compared using the McNemar or chi-square and Wilcoxon tests, respectively. In addition, each group’s usability scores and grades will be correlated using Spearman correlation.
**Secondary**				
	Perception of AI^c^	Continuous, nominal, ordinal, and 5-point Likert-type scale	The questionnaire consists of four sections: (1) sociodemographic information; (2) AI literacy exploration of positive learning experiences with AI; (3) examination of negative experiences associated with AI use; and (4) an assessment of the potential for discussing accountability, fostering student leadership, and addressing ethical and equity concerns pertaining to the use of AI.	Fisher exact or Pearson chi-square test will investigate the associations between the categorized scales and sociodemographic characteristics.
Learning outcomes		Continuous	Students’ grades on both interventions. Score range (0-100)	Mean, SD

^a^SUS: System Usability Scale.

^b^5=Strongly agree, 4=agree, 3=neither agree nor disagree, 2=disagree, and 1=strongly disagree.

^c^AI: artificial intelligence.

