## Introduction

### Background

The integration of artificial intelligence (AI) into the education field has led to many possibilities, benefiting both educators and students [1]. AI takes on various roles as an intelligent tutor, a collaborative learning partner, a valuable tool, and even an adviser in influencing educational policies [2,3]. The multidimensional role of AI in education, as demonstrated by the potential for dynamic and adaptive learning experiences, aligns with ChatGPT’s capacity to operate as a valuable educational tool. ChatGPT is a generative AI that can generate complex answers to questions asked by the user. It has been described as a tool offering numerous benefits in the field of education [4]. It serves as a platform for enhancing students’ writing skills through features such as text completion, translation, and summarization tools. Educators can integrate ChatGPT into their courses to customize the learning journey for their students by considering their preferred learning methods and existing proficiency levels [4].

An exploratory survey examining the use of ChatGPT in various domains, including education, health care, and research, revealed both positive and negative impacts [5]. On the positive side, ChatGPT was found to level the playing field for students facing language challenges, enhance comprehension by providing additional details, and offer valuable assistance in crafting writing assignments. However, the study also uncovered negative consequences, such as the potential for inaccuracies, concerns about replacing hard work with automated solutions, and the possible discouragement of critical thinking skills. In addition, questions remained regarding academic integrity and students’ willingness to disclose their use of ChatGPT. These findings emphasize the need for careful consideration and guidance when integrating AI technologies such as ChatGPT into various fields [5].

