### Study Objectives

#### Primary Objectives

We aim to explore the usability and effectiveness of ChatGPT compared with conventional web-based tools as a supplementary assistance tool to enhance undergraduate health sciences students’ learning experiences and outcomes.

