#### Secondary Objectives

Our secondary objectives are to (1) explore students’ perceptions and experiences with ChatGPT as a learning tool; (2) explore the potential benefits of or barriers to using ChatGPT to improve students’ writing abilities in the health sciences; and (3) investigate students’ perceptions of accountability, ethical considerations, and equity concerns related to the use of AI in education.

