### Intervention and Measurement

During the initial phase of the study, participants assigned to sequence AB will use ChatGPT (experimental intervention: group A) to complete their assignments, while participants assigned to sequence BA will use conventional web-based tools (control intervention: group B) and serve as a control group. In the subsequent period, the interventions will switch between the 2 groups. Students will not know which one is the “intervention of interest” and which one will be the “comparator.” As mentioned above, the learning activity to be assessed in this project is part of the mandatory course activities. This means that all students will receive a grade for this assignment. Therefore, the instructor will not be able to determine which students have or have not participated in the study. Students’ acceptance to participate in this study only gives permission to the research team to use their data for research purposes, but all students will be assessed for this work as part of the course. The course instructor will not be responsible for grading the assignments associated with the intervention. The TA will be responsible for grading assignments and assigning a unique number code to each participating student, which will be linked to their names. This coded information will be sent to the RA to preserve anonymity throughout the process. The RA will receive the graded assignments, the student names, and their respective codes from the TA. The RA will collect the grades of the student participants and submit them to the research team members responsible for the analysis. It is important to note that the research team, which includes the course instructor, will not have access to the participants’ names. Only the grades and the participant codes will be accessible for analysis. The research team, including the course instructor, will perform the data analysis based solely on the provided grades and participant codes, without access to any identifiable information. This further ensures that anonymity is strictly maintained throughout the analysis phase.

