### Experimental Intervention

In this study, the intervention of interest is the use of ChatGPT by students to complete their assignments. As part of this intervention, students will be given a period of 6 days to use it for assignment completion. Along with the assignment instructions, participants will receive an ethical guideline and specific guidelines on how to use ChatGPT effectively (Multimedia Appendices 1 and 2) [18-23].

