### Control Intervention

In this study, the control intervention is the use of conventional web-based tools by students to complete the assignment. In this intervention, they will receive instructions on how to complete the assignment using conventional web-based tools available on the internet, without the use of ChatGPT or other generative AI platforms “and” or “or” tools. They will have a timeframe of 6 days to complete the assignment using these conventional web-based tools. Similar to the participants in the experimental intervention, they will also be required to fill out a survey on technology usability, providing feedback on their experience with the web-based tools.

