## Results

Data collection took place in October and November 2023; the anticipated results are scheduled for publication in 2024. We anticipate several key findings. First, randomization is expected to have groups with closely matched demographic characteristics, ensuring a balanced starting point for our analysis. Second, we anticipate that usability will be significantly higher for the ChatGPT intervention than for conventional methods, reflecting the potential benefits of AI-assisted learning. In addition, regarding ChatGPT’s use in assignments, we expect to observe students expressing concerns about data privacy and plagiarism, consistent with prior literature findings on these issues. The potential correlation between usability and learning outcomes is a significant aspect to consider in our study. Understanding how usability impacts learning outcomes not only is critical for this study but also lays the foundation for future investigations. By quantifying the effect sizes of both the learning and usability effects in this study, we can better inform the calculation of sample sizes for larger RCTs on this topic. These data will be invaluable for designing robust experiments and ensuring that our research can provide meaningful insights into the relationship between usability and educational outcomes.

Furthermore, it is our anticipation that despite these concerns, learning outcomes will remain consistent across both interventions. We expect to observe that while these concerns may be raised, the overall effectiveness and educational benefits of ChatGPT are not compromised. Our study seeks to determine whether these anticipated results are confirmed. These data will contribute to a better understanding of the potential impacts of integrating AI into health sciences education.

This study is expected to contribute to the identification of key areas and challenges concerning the use of AI as an educational tool, specifically examining its benefits and challenges for students. By doing so, it aims to facilitate the establishment of comparable frameworks for future academic endeavors. In addition, the findings will enlighten educators about the potential advantages and barriers associated with integrating AI into educational activities for university students.

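### The 'learning outcomes' endpoint is the grade on work done with the assigned tool, so it measures tool-assisted assignment performance and should be named and interpreted that way

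*Protocol article*

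**What the plan says.** Table 1 gives one measure for learning outcomes: "Students’ grades on both interventions. Score range (0-100". Intervention and Measurement explains that the activity is a mandatory course assignment: "This means that all students will receive a grade for this assignment".

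The two intervention sections say how the graded work is made. Under Experimental Intervention, "the intervention of interest is the use of ChatGPT by students to complete their assignments". Under Control Intervention, "the control intervention is the use of conventional web-based tools by students to complete the assignment", with generative AI not allowed. Students have 6 days in either condition.

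Outcomes and Measurements sets two collection points, one after each intervention. The other two outcomes, the System Usability Scale (SUS) and the perception survey, are self-reported.

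The aims are worded in terms of learning. Primary Objectives describes ChatGPT "as a supplementary assistance tool to enhance undergraduate health sciences students’ learning experiences and outcomes". The exploratory hypothesis is that learning outcomes differ between the tools, and Data Analysis speaks of effects of the intervention on learning outcomes. Results anticipates that learning outcomes will be consistent across the interventions and that "the overall effectiveness and educational benefits of ChatGPT are not compromised". The Discussion overview expects similar learning outcomes in both groups.

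**The concern.** A grade on a finished assignment reflects the student and whatever the student used to produce it. The tools differ in how much of the text they can supply. Background describes ChatGPT as able to generate complex answers and to complete and summarize text, and the control condition excludes tools of that kind. A grade comparison between the periods is therefore partly a comparison of the tools' output.

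The Background also reports, from an earlier survey, "concerns about replacing hard work with automated solutions, and the possible discouragement of critical thinking skills". A student who learned less but handed in a good assisted text would receive a good grade, so this endpoint could not reveal such an effect.

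At stake is what the trial may conclude. If grades turn out similar, as the article expects, the natural report is that learning was preserved. Educators are the intended readers of that statement, and the data would not support it.

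**Working it through.** The article gives no figure on this point to reproduce. Its only computed figure, the sample size of 45 raised to 50, does not enter, because no number of students changes what the grade measures. The check sets the provisions side by side.

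1. **What is scored.** Table 1: the grade, 0 to 100, in each period. No other measure is listed under learning outcomes.
2. **How the scored work is made.** Experimental Intervention and Control Intervention: with the assigned tool, in both periods. Both grades are therefore tool-assisted, by different tools.
3. **When it is measured.** Outcomes and Measurements: once after each intervention. No knowledge test, writing task or retention test without the tool is listed.
4. **What the contrast identifies.** As a simplification, write each grade as a student part *L* plus a tool part *T*. With A for ChatGPT and B for conventional tools, the within-student contrast is

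   D = (L_A − L_B) + (T_A − T_B).

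   The trial observes D only. There is one equation and two unknown differences. If D = 0, then L_A − L_B = −(T_A − T_B). Equal grades are then compatible with equal learning, less learning offset by a larger tool contribution, or more learning offset by a smaller one. If D > 0, the sign of L_A − L_B is still undetermined. The additive form is only for illustration; any form in which both parts affect the grade leads to the same result.
5. **What follows for the correlation.** Data Analysis correlates usability scores with grades in each group. A tool that is easy to use and also contributes good content could produce a positive correlation without any change in learning.
6. **How the design fits.** Washout Period uses 21 days and a new topic of similar complexity to reduce memory and lingering effects of the first period. Lasting knowledge or skill is itself a lingering effect and would appear as carryover. Task performance with the tool in hand is the kind of effect that can start and stop with each period. The crossover is coherent for that reading.
7. **Whether the limit is acknowledged.** Limitations and Strengths lists sample size and generalizability, the short intervention and long-term effects, restriction to one AI tool, and self-report bias. It does not say that the grade is taken on assisted work.

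**The case against.** The strongest reply is that the measure is openly stated and subordinate. Usability is the primary outcome, learning outcomes are secondary, and their hypothesis is labelled exploratory and tied to completing assignments. A course grade is a legitimate measure of assignment performance. This stands, and it is why the remedy is a change of name and claim. It does not remove the point, because Primary Objectives, Data Analysis, Results and the Discussion overview drop the narrower sense and speak of learning.

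The sentence in Results about benefits not being compromised follows a mention of privacy and plagiarism concerns, and the article says the study will determine whether its expectations are confirmed. That is fair. Even so, the adjoining expectation of consistent learning outcomes could be checked only against the grades.

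The article also says it captures immediate impacts and may miss long-term effects. This covers retention but not immediate learning without the tool.

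The two appendices with guidance on using AI are not shown, nor are the grading criteria. They may limit how much generated text enters the submission. The work would still be done with the tool.

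Three stronger readings are tempting but unsupported:

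- *The grade favours ChatGPT.* No figure supports a direction. The Introduction also reports inaccurate content, which could lower grades, and the control work is assisted too.
- *The trial fails its writing objective.* That objective is to "explore the potential benefits of or barriers to using ChatGPT to improve students’ writing abilities in the health sciences". It is exploratory, the surveys and later focus groups can describe perceived benefits and barriers, and nowhere is the grade said to measure writing ability.
- *A baseline measure is missing.* In a randomized crossover each student serves as their own control, so comparing the conditions needs none.

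**Conclusion.** The point holds in a limited form. As defined, the endpoint estimates the difference in tool-assisted assignment performance between ChatGPT and conventional tools. It does not isolate student learning, and neither similar nor higher grades would establish that learning or educational benefit was preserved or improved.

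It reaches one of the three listed outcomes, the exploratory hypothesis and the usability-grade correlation, together with the conclusions drawn from them. The primary usability outcome is untouched. No size in grade points can be given, and the direction of any distortion is unknown.

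The conclusion rests on two readings of the text: that the grade is the only performance measure of learning, as Table 1 states, and that it is awarded for the assignment produced with the tool, as the intervention sections state.

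**What to change.** Rename the outcome *tool-assisted assignment performance (grade)* in Study Hypotheses, Outcomes and Measurements, Table 1, Data Analysis, Results and the Discussion overview. The Abstract uses the same label and should follow. Limit the exploratory hypothesis, the usability-grade correlation and all conclusions to that outcome, and read the learning part of the primary objective in the same sense. Add to Limitations and Strengths that knowledge or learning without the tool was not measured.

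This needs wording only and leaves data collection and the planned tests unchanged. The price is a more modest conclusion.

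Adding unaided test items to the surveys is not a remedy here. Results states that data collection took place in October and November 2023. Items in an unsupervised web survey would not be reliably unaided, and the perception survey is sent only after the ChatGPT period. An unaided assessment is a matter for a future trial, where a lasting effect would be compared most cleanly between sequences after the first period.
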